**Fig. 2 Fig2:**
[figure not shown]
Standard Protocol Items: Recommendation for Interventional Trials (SPIRIT) figure. * X is 1–21 days. ** Y is a period after the end of the post-discharge follow-up. *** Interventional period. **** Observational period. AMO admission medication order, BPMH best possible medication history

### Outcomes

The primary outcome will assess the rate of patients having at least one preventable medication error (e.g. omission, wrong dose, wrong route of administration, etc.) on admission medication order (AMO). The primary outcome will be evaluated by clinical pharmacists retrospectively in the control period and prospectively in the interventional period.

Among the secondary outcomes, the potential clinical impact of each error detected will be assessed by a hospital physician and two clinical pharmacists (different from the investigators) by using a decision algorithm [30] adapted from the NCC MERP’s Index [31] and employing the high alert risk medication list of the Institute of Safe Medication Practices [32] and the North Carolina Narrow Therapeutic Index [33]. All of the experts, who are seniors specialized in geriatrics, will blindly perform the analysis, i.e. without knowing the hospital center concerned, after completion of patient recruitment for all the centers. The potential clinical impact will also be evaluated by the rate of patients at high risk of ADEs according to Trivalle’s score [9, 34].

Other secondary outcomes will be: (1) the acceptance rate of pharmaceutical interventions during the interventional period; (2) the readmission and mortality rates 30 and 90 days after discharge; (3) the length of hospital stays; (4) the satisfaction of care providers involved in the collaborative pharmaceutical care (assessed by postal or electronic mail after the end of the 90-day follow-up); and (5) the induced and avoided costs of the strategy. For this last outcome, we will estimate the induced costs by measuring the time spent performing the collaborative pharmaceutical care. We will also assess the avoided costs by estimating the healthcare consumptions dues to medication errors by using the results of a French national study concerning ADE occurrence and cost [1] and/or by using an expert concertation via a DELPHI method.

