### Setting and population

Six French University Hospitals which benefit from a strong expertise in clinical pharmacy and are dispersed across the country have agreed to participate (Table 1). Each center selected a short-term care unit in a medical specialty which welcomes the elderly. Only units in which there was no clinical pharmacist were eligible. The medical heads of all the units selected agreed to participate in the study.

All healthcare participants volunteered to participate in the study. In each center, two pharmacy students or two pharmacy technicians will participate in the control period (Table 1); two senior clinical pharmacists will participate in the interventional period. In each hospital center, the same clinical pharmacists will detect medication errors in both periods. All the participants benefited from a specific centralized training in order to harmonize their practices in each period. This training was performed over three days, the week before the study started. After data collection, controls will be carried out to ensure that pharmaceutical interventions have not been misclassified.

Patients aged at least 65 years, hospitalized in one of the participating care units, and having given their agreement to be called for a 30-day and 90-day follow-up could be enrolled. In each 14-day period, 15 patients will be recruited in each care unit no more than 24 h or 48 h after admission, respectively, in the week or weekend/public holiday. Finally, a total of 630 patients will be enrolled in the study. We will exclude patients with a hospital stay > 21 days, as there is a risk of there being too many medication modifications during the hospital stay.

The study procedures and assessments are outlined in the Standard Protocol Items: Recommendation for Interventional Trials (SPIRIT) checklist (see Additional file 1) and SPIRIT Figure (Fig. 2).

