### Intervention

The flow of the intervention is outlined in Fig. 3. During the control period, there will be no clinical pharmacist in the care unit. The hospital physician will write the AMO, then a pharmacy technician or a pharmacy student will perform the best possible medication history (BPMH) according to the SOP MED’REC [35] and collect all the relevant bioclinical data to perform prescription review. No information will be transmitted to the healthcare team except in life-threatening emergencies. A clinical study technician from the promoter center will call all the patients at 30 ± 10 and 90 ± 10 days after their hospital discharge to determine whether they had died or been re-hospitalized. If they report that they had been re-hospitalized, a pharmacy resident from the promoter center will call them again to investigate if the cause of the hospitalization is due to medication regimen. After the follow-up, the medication reconciliation and review will be retrospectively conducted by the clinical pharmacists who have participated in the interventional period in each investigator center. Finally, experts will retrospectively assess the potential clinical harm of each medication error detected.

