**Fig. 3 Fig3:**
[figure not shown]
MEDREV study - flow of the intervention. BPMH, best possible medication history

In the interventional period, a senior clinical pharmacist based in the care unit will perform medication reconciliation by comparing the BPMH to the AMO and notifying the prescriber of any possible discrepancies. He/She will collect all relevant bioclinical data and perform medication review of the AMO by using the STOPP and START tools [18], the French list of potentially inappropriate medications in elderly [36], and the PAPA guide about medication prescription adapted to the elderly, published by the French Society of Geriatric and Gerontology [37]. The clinical pharmacist will have a collaborative meeting with both the prescriber and the nurse in order to notify any possible medication errors and suggest any proposals to optimize the AMO according to the medical history, the clinical status, and the therapeutic adherence etc. (e.g. change of galenic form due to swallowing problem, dose adjustment to renal function, etc.). After the collaborative meeting, the clinical pharmacist will check whether the prescriber has accepted his/her suggestion(s) and modified the AMO. All the pharmaceutical interventions, i.e. the medication errors detected and the pharmaceutical suggestions of order modification, will be collected and characterized in a standardized form according to the French Society of Clinical Pharmacy [38]. The post-discharge follow-up and the retrospective assessment of the potential harm of each error will be performed as in the control period. At the end of the study, a satisfaction survey will be sent to all the care providers involved in the collaborative pharmaceutical care.

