### Limitations and potential bias

Due to the retrospective nature of the pharmaceutical evaluation during the control period, an information bias may lead clinical pharmacists not to notify a pharmaceutical intervention or, on the contrary, to carry out an irrelevant pharmaceutical intervention. Although this bias cannot be controlled by the prescribing physician's opinion because of the retrospective mode, the relevance of these interventions will be evaluated by experts who will rate clinical criticality. In addition, in order to avoid contamination bias, the retrospective assessment will not start until after the end of the control period in each hospital.

Telephone calls to collect deaths and potential re-hospitalizations are also limited. They will be carried out by a semi-directive interview but will remain based on the patient’s statement, which may omit intentionally or unintentionally to communicate some information. It may therefore be subject to a potential information bias that should be comparable between the two periods. It should be noted, however, that the reason for hospitalization will be collected in an exploratory manner as part of a secondary criterion.

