### Blinding

Due to the nature of the intervention, blinding will be not possible for patients and care providers. Therefore, this study is fully open, without reliable blinding. The only blinded outcome is a secondary one: the expert committee in charge of assessing the potential clinical impact of the medication errors detected will not know the period and the center concerned by each medication error detected.

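### How primary-outcome errors are found changes with treatment in every unit, and the masked expert panel meant to guard against this feeds only a secondary outcome

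*Protocol article*

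**What the plan says.** The primary outcome is the proportion of patients with at least one preventable medication error on the admission medication order (AMO). The Outcomes section states: "The primary outcome will be evaluated by clinical pharmacists retrospectively in the control period and prospectively in the interventional period".

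The Intervention section describes the two procedures:

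- **Control.** A technician or student takes the best possible medication history (BPMH) under a standard operating procedure and collects the bioclinical data. Errors are judged later: "After the follow-up, the medication reconciliation and review will be retrospectively conducted by the clinical pharmacists who have participated in the interventional period".
- **Interventional period.** A senior pharmacist based in the unit compares the BPMH with the AMO. "He/She will collect all relevant bioclinical data and perform medication review of the AMO". The pharmacist then meets the prescriber and the nurse, and afterwards checks whether the order was changed.

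Under Setting and population: "In each hospital center, the same clinical pharmacists will detect medication errors in both periods". The Blinding section says "Therefore, this study is fully open, without reliable blinding", and adds: "The only blinded outcome is a secondary one".

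The Limitations section accepts that retrospective assessment may lead pharmacists to miss relevant interventions or to record irrelevant ones. It says that, although this bias is beyond control through the prescriber's "opinion because of the retrospective mode, the relevance of these interventions will be evaluated by experts who will rate clinical criticality".

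**The concern.** Three features of ascertainment change together on the day a unit switches: who gathers the data, when the errors are judged, and whether the prescriber can be consulted. The judges know the period and have a stake in the result, since they deliver the intervention. Any difference in how readily errors are found, or how readily a non-error is labelled as one, is added to the treatment contrast.

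The safeguard named in the Limitations section does not reach the primary outcome. The experts rate the potential clinical impact of errors already detected, and that rating is a secondary outcome. Neither the Outcomes section nor the Statistical analysis section says that it decides whether an error counts. At stake is whether the primary contrast can be attributed to pharmaceutical care rather than partly to a change in measurement.

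**Working it through.** **1. The plan's own power figure.** Inputs from Sample size calculation: 6 units, 7 periods, 15 patients per unit-period, difference 0.30, variance 0.20, intra-class correlation 0.05. Two-sided alpha of 0.05 is an assumption, as none is stated. The Hussey-Hughes variance is

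Var = I·s²(s² + Tτ²) / [(IU − W)s² + (U² + ITU − TW − IV)τ²]

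- I = 6, T = 7, U = 21 treated unit-periods, W = V = 91
- s² = 0.95 × 0.20/15 = 0.01267; τ² = 0.05 × 0.20 = 0.01
- IU − W = 35; U² + ITU − TW − IV = 441 + 882 − 637 − 546 = 140
- Var = 6 × 0.01267 × 0.08267 / (35 × 0.01267 + 140 × 0.01) = 0.00341, so SE = 0.0584
- Power = Φ(0.30/0.0584 − 1.96) = 99.9%

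This is consistent with the stated 99%. Power is not the problem. A precise design makes a detection artefact easier to declare significant.

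**2. Can the model separate detection from treatment?** The linear predictor in Statistical analysis contains an intercept, a group indicator and a cluster random effect. An indicator for detection method would equal the group indicator for every patient, because the method changes when treatment changes. The two effects are not separately identifiable. Randomising the switch time, adding period terms or enrolling more patients would not alter that.

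**3. Illustration of size.** Every sensitivity and false-positive rate below is an assumption; the documents give none. With true rate p, sensitivity Se and false-positive rate f among error-free patients,

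observed rate = p·Se + (1 − p)·f

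Take p = 0.46 (the control rate in Sample size calculation) in both periods, so there is no true effect.

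*Sensitivity gap only (f = 0).* The spurious difference is 0.46 × gap. The last two columns give the chance of a significant result under the SE above, and under a linear analogue of the written model, which has no period term (SE 0.039).

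| Se, one period vs the other | Spurious difference | With period terms | Without |
|---|---|---|---|
| 0.9 vs 0.8 | 4.6 points | 12% | 22% |
| 0.9 vs 0.7 | 9.2 points | 35% | 66% |
| 0.9 vs 0.6 | 13.8 points | 66% | 94% |

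The sign depends on which period detects less.

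*Both mechanisms together.* Suppose control has Se 0.80 and f of 0.05 to 0.15, and the interventional period has Se 0.95 and f = 0.

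- Control: 0.46 × 0.80 = 36.8%, plus 0.54 × 0.05 = 2.7 to 0.54 × 0.15 = 8.1 points, giving 39.5% to 44.9%
- Interventional: 0.46 × 0.95 = 43.7%
- Control minus interventional: −4.2 to +1.2 points

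The mechanisms partly cancel, and the sign changes within the assumed range.

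**4. With a true effect as planned** (46% vs 46 − 30 = 16%, f = 0). Se 0.9 in control and 0.7 in the interventional period gives 0.414 − 0.112 = 30.2 points. Se 0.7 and 0.9 gives 0.322 − 0.144 = 17.8 points.

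**The case against.** The protocol is not careless here. Keeping the pharmacist off the ward in control follows from the contamination concern in the Design section. The same pharmacists judge both periods, all staff had three days of central training, the control BPMH follows a standard procedure, and checks for misclassified interventions are planned after data collection. The Limitations section already discloses both missed and irrelevant findings, so no further limitation statement is needed.

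These measures reduce differences between assessors. They do not mask the assessors or align timing, data collector and prescriber access. The misclassification checks are not described as masked or as searching again for errors.

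A reader might infer more than the text supports:

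- **That the bias favours the intervention.** The article names both over- and under-detection in control, and the combined illustration changes sign.
- **That intended discrepancies are dropped from the interventional count once the prescriber answers.** The remark on the prescriber's opinion makes this plausible, but no counting rule says so. All pharmaceutical interventions are to be recorded, with acceptance checked separately.
- **That control is judged by chart review alone.** A dedicated BPMH and bioclinical data are collected during the stay for that review.
- **That the pharmacist's error list should be locked before the collaborative meeting.** With 622 of 630 patients enrolled (Trial status), this is too late for nearly all. It could also count only errors not yet corrected, and so remove the effect under study if the outcome is meant to reflect corrected orders.

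**Conclusion.** The concern holds in limited form. The primary outcome is judged unmasked, by those who deliver the intervention, under a procedure that changes with treatment in every unit. The analysis cannot separate the two effects, and the one masked assessment is not tied to the primary outcome. These points rest on the text alone.

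The size and net direction are undetermined. The figure of 4.6 points per 10-point sensitivity gap assumes a true rate of 46% and no false positives. Gaps of this kind could distort the estimate, but nothing in the documents shows that they would produce or abolish a 30-point difference.

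**What to change.** Use the existing panel of one physician and two pharmacists.

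1. For every detected error in the standardized form, the panel records whether it is a confirmed preventable medication error on the AMO.
2. The panel judges from one standard record in both periods: BPMH, AMO and bioclinical data. The prescriber's response, acceptance and dates are removed, as is anything showing who collected the data.
3. The panel is masked to period and center. The Outcomes section explains the masking by center only, while the Blinding section says both; reconcile them.
4. Panel-confirmed errors define the primary outcome, or at least a prespecified sensitivity analysis of it.
5. Whether errors are counted before or after correction of the order follows the rule used for the primary outcome, and is handled separately from the panel.

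The cost is one yes/no field on a review that already covers each detected error, plus preparation of the stripped records. No new staff are needed. It is still feasible because the panel works after recruitment is complete. The drawback is that confirmation removes false positives but does not recover errors missed in either period.

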### Intervention

The flow of the intervention is outlined in Fig. 3. During the control period, there will be no clinical pharmacist in the care unit. The hospital physician will write the AMO, then a pharmacy technician or a pharmacy student will perform the best possible medication history (BPMH) according to the SOP MED’REC [35] and collect all the relevant bioclinical data to perform prescription review. No information will be transmitted to the healthcare team except in life-threatening emergencies. A clinical study technician from the promoter center will call all the patients at 30 ± 10 and 90 ± 10 days after their hospital discharge to determine whether they had died or been re-hospitalized. If they report that they had been re-hospitalized, a pharmacy resident from the promoter center will call them again to investigate if the cause of the hospitalization is due to medication regimen. After the follow-up, the medication reconciliation and review will be retrospectively conducted by the clinical pharmacists who have participated in the interventional period in each investigator center. Finally, experts will retrospectively assess the potential clinical harm of each medication error detected.

**Fig. 3 Fig3:**
[figure not shown]
MEDREV study - flow of the intervention. BPMH, best possible medication history

In the interventional period, a senior clinical pharmacist based in the care unit will perform medication reconciliation by comparing the BPMH to the AMO and notifying the prescriber of any possible discrepancies. He/She will collect all relevant bioclinical data and perform medication review of the AMO by using the STOPP and START tools [18], the French list of potentially inappropriate medications in elderly [36], and the PAPA guide about medication prescription adapted to the elderly, published by the French Society of Geriatric and Gerontology [37]. The clinical pharmacist will have a collaborative meeting with both the prescriber and the nurse in order to notify any possible medication errors and suggest any proposals to optimize the AMO according to the medical history, the clinical status, and the therapeutic adherence etc. (e.g. change of galenic form due to swallowing problem, dose adjustment to renal function, etc.). After the collaborative meeting, the clinical pharmacist will check whether the prescriber has accepted his/her suggestion(s) and modified the AMO. All the pharmaceutical interventions, i.e. the medication errors detected and the pharmaceutical suggestions of order modification, will be collected and characterized in a standardized form according to the French Society of Clinical Pharmacy [38]. The post-discharge follow-up and the retrospective assessment of the potential harm of each error will be performed as in the control period. At the end of the study, a satisfaction survey will be sent to all the care providers involved in the collaborative pharmaceutical care.

### Limitations and potential bias

Due to the retrospective nature of the pharmaceutical evaluation during the control period, an information bias may lead clinical pharmacists not to notify a pharmaceutical intervention or, on the contrary, to carry out an irrelevant pharmaceutical intervention. Although this bias cannot be controlled by the prescribing physician's opinion because of the retrospective mode, the relevance of these interventions will be evaluated by experts who will rate clinical criticality. In addition, in order to avoid contamination bias, the retrospective assessment will not start until after the end of the control period in each hospital.

Telephone calls to collect deaths and potential re-hospitalizations are also limited. They will be carried out by a semi-directive interview but will remain based on the patient’s statement, which may omit intentionally or unintentionally to communicate some information. It may therefore be subject to a potential information bias that should be comparable between the two periods. It should be noted, however, that the reason for hospitalization will be collected in an exploratory manner as part of a secondary criterion.

### Blinding

Due to the nature of the intervention, blinding will be not possible for patients and care providers. Therefore, this study is fully open, without reliable blinding. The only blinded outcome is a secondary one: the expert committee in charge of assessing the potential clinical impact of the medication errors detected will not know the period and the center concerned by each medication error detected.

### Sample size calculation

A stepped wedge trial was designed according to a validated methodology [39]. A previous study showed that the rate of patients with at least one medication error in the AMO was 46% and 2% for the control and experimental strategies, respectively [11]. In order to make more conservative assumptions, we decreased the expected difference from 0.44 to 0.30. The variance of the difference deducted was 0.20. The intra-class correlation coefficient was unknown but was assumed equal to 0.05 in the most conservative case. In each 14-day period, each investigator hospital center will recruit 15 patients, i.e. a total of 630 patients for the seven periods and the six hospital centers. These assumptions led to a statistical power estimated at 99% [39]. The required power was maximal in order to potentially perform subgroup analyses when justified.

### Monitoring

A monitoring committee will meet after the start of the study, every 15 days for the first month, and then every month. A clinical research associate delegated by the promoter will monitor the study in accordance with the regulations in force. It will be responsible for monitoring the rate of inclusions and alerting to possible deviations from the protocol. Bi-monthly newsletters will be sent to all study participants.

The investigator shall inform the vigilance unit at Nîmes University Hospital of any expected or unexpected serious adverse events (SAE) and any new events that may affect the safety of persons subject to research as soon as they become aware of them. Reports of expected and unexpected SAEs are made by completing a dedicated report form and sending it by fax or e-mail.

